## Abstract

**Background:**

Anthracycline chemotherapy (AC) is an efficacious (neo) adjuvant treatment for early-stage breast cancer (BCa), but is associated with an increased risk of cardiac dysfunction and functional disability. Observations suggest that regular exercise may be a useful therapy for the prevention of cardiovascular morbidity but it is yet to be interrogated in a large randomised trial.

The primary aims of this study are to: *1)* determine if 12-months of ET commenced at the onset of AC can reduce the proportion of BCa patients with functional disability (peak VO_2_, < 18 ml/kg/min), and *2)* compare current standard-of-care for detecting cardiac dysfunction (resting left-ventricular ejection fraction assessed from 3-dimensional echocardiography) to measures of cardiac reserve (peak exercise cardiac output assessed from exercise cardiac magnetic resonance imaging) for predicting the development of functional disability 12-months following AC. Secondary aims are to assess the effects of ET on VO2peak, left ventricular morphology, vascular stiffness, cardiac biomarkers, body composition, bone mineral density, muscle strength, physical function, habitual physical activity, cognitive function, and multidimensional quality of life.

**Methods:**

One hundred women with early-stage BCa (40–75 years) scheduled for AC will be randomized to 12-months of structured exercise training (*n* = 50) or a usual care control group (*n* = 50). Participants will be assessed at baseline, 4-weeks following completion of AC (4-months) and at 12-months for all measures.

**Discussion:**

Women diagnosed with early-stage BCa have increased cardiac mortality. More sensitive strategies for diagnosing and preventing AC-induced cardiovascular impairment are critical for reducing cardiovascular morbidity and improving long-term health outcomes in BCa survivors.

**Trial registration:**

Australia & New Zealand Clinical Trials Registry (ANZCTR), ID: 12617001408370. Registered on 5th of October 2017.

## Background

Breast cancer (BCa) is the most commonly diagnosed cancer among women, with over 1.6 million women diagnosed globally each year [1]. Advances in detection and treatment have improved cancer-specific survival such that the 5-year survival rate is now approaching 90% [2, 3]. An unexpected consequence of this success is that early stage BCa survivors are as likely to die of cardiovascular (CV) causes as they are from BCa [4–6]. This may be due to a combination of common cardiac risk factors combined with toxicity from cancer therapies, particularly anthracycline chemotherapy (AC) [7, 8]. Whilst AC is one of the mainstays of neoadjuvant and adjuvant therapy for triple-negative and locally-advanced BCa [9], it induces dose-dependent CV injury causing reductions in functional capacity (measured objectively as a peak oxygen uptake, peak VO_2_, < 18 ml/kg/min) that is associated with an increased risk of heart failure (HF) [10]. AC-mediated cardiac dysfunction shows limited reversibility with pharmacological treatment, particularly if detected late [11]. Furthermore, those who go on to develop symptomatic HF experience poor mortality outcomes [12]. As such there is an emphasis on detecting cardiac dysfunction at the earliest possible stage.

Findings from a meta-analysis indicated that time since treatment is an important risk factor for cardiotoxicity [13]. Indeed, the discrepancy between the rates of cardiac dysfunction detected soon after treatment and long-term heart failure incidence [10] highlights that an absence of measurable cardiac dysfunction soon after treatment does not adequately predict the risk of subsequent toxicity. This also emphasises the need for improved early detection strategies [14, 15]. Currently, the cornerstone for detecting AC-induced cardiac dysfunction is measuring changes in resting left-ventricular ejection fraction (LVEF) [14–17]. Whilst LVEF has been in use for decades, its ability to predict subsequent cardiotoxicity is limited by poor reproducibility [18, 19], load and heart rate dependence, and the current LVEF-based classification for cardiotoxicity (typically a > 10% drop from baseline to a value < 50–53%) shows weak associations with heart failure outcomes [20, 21]. Furthermore, half of HF patients have preserved LVEF (> 50%), highlighting that LVEF is insensitive to clinically significant cardiac dysfunction [22]. Consequently, there is growing interest in alternative measures for early detection of cardiac dysfunction following AC [15, 16].

The assessment of an individual’s VO_2_peak has been recently endorsed by the American Heart Association as an important primary endpoint for individuals with- or at risk of HF [23] as it can capture the degree of impairment along the oxygen cascade [24], whilst providing meaningful information on functional capacity [24, 25], and HF incidence [26, 27], and prognosis [28, 29]. The functional impact of cardiotoxic BCa treatments may be quantified using cardiopulmonary exercise testing as a VO_2_peak below 18.0 mL/kg/min, which is indicative of ‘functional disability’ given its approximation to the level of fitness required to perform simple activities of daily living [25]. This threshold is associated with a 7–9 fold increase in the risk of heart failure [26, 30], and a two-fold increased risk of all-cause mortality in metastatic BCa survivors [31]. Importantly, as many as 29–50% of BCa survivors fall below this threshold despite having a normal resting LVEF [31, 32], highlighting the need for better diagnostic approaches. Some of the key limitations of resting LVEF for predicting functional disability and HF risk could be overcome through the assessment of cardiac reserve, defined as the increase in cardiac function from rest to peak exercise. This is based on the premise that symptoms of HF typically present with minimal levels of exertion, when the heart has insufficient reserve to adequately respond to the demands of exercise. The use of cardiac imaging is advantageous as it provides a specific assessment of cardiac reserve. Whilst posing several technical challenges, the development of novel imaging techniques such as exercise cardiac magnetic resonance imaging (ExCMR) allows for the assessment of biventricular function with a high degree of accuracy [33], and may provide a more meaningful understanding of heart failure risk and functional capacity in BCa survivors than resting LVEF [32].

Current approaches for preventing cardiovascular morbidity in patients receiving anthracyclines include treatment withdrawal and/or modification, and pharmacological strategies. Treatment withdrawal prevents further cardiac injury, however is problematic due to the potential negative effects on cancer-related outcomes [34]. The use of pharmacotherapies such as Dexrazoxane [35, 36], angiotensin converting enzyme inhibitors [35], and beta-blockers [35] can reduce the risk of subsequent cardiac dysfunction. However, this appears at odds with the current trend towards personalized therapy, given that this would result in the majority of patients being treated unnecessarily. Additionally, given cardiac function is unlikely to be the sole driver behind AC-induced impairments in exercise capacity and functional disability [37], the ability of cardiac-focused pharmacotherapy to completely reverse a patient’s exercise intolerance may be limited. Exercise training (ET) has emerged as an important therapeutic tool for addressing a number of adverse effects associated with cancer treatment [38], and there is growing interest in its use for preventing cardiotoxicity and functional disability [39]. However, whilst exercise can prevent or attenuate declines in VO_2_peak during BCa chemotherapy (predominantly anthracycline-based) [38, 40–42], no randomised trials have investigated whether it can reduce the incidence of important clinical endpoints such as functional disability. Furthermore, the degree to which the beneficial effects on VO_2_peak reflects cardiac versus peripheral ‘protection’ is still unknown and will have important implications for the cardioprotective role of exercise. The primary trials investigating the effect of exercise training on cardiac function during AC have shown neither a beneficial, nor detrimental effect on cardiac function [32, 40, 43]. These studies have been small, short-term and the majority have relied on resting measurements of cardiac function to identify cardiac dysfunction. Thus, there is a need for larger, longer RCTs that are based on outcomes that are more sensitive to cardiac dysfunction and prognosis.

Therefore, in women with BCa undergoing anthracycline-based chemotherapy, this 12-month RCT has two primary aims:
To compare the current standard-of-care (resting LVEF) to measures of cardiac reserve (peak exercise cardiac output; Qc) as predictors of functional disabilityTo determine whether a 12-month structured exercise training (ET) program reduces the proportion of BCa patients who are functionally disabled 12-months after the initiation of AC.

We hypothesize that:
Cardiac reserve will be superior to resting LVEF at predicting the development of functional disability 12-months following ACParticipating in a 12-month structured ET will reduce the proportion of patients who are functionally disabled 12-months following AC.

Secondary aims include assessing the effect of ET on changes in cardiopulmonary fitness and cardiac reserve, along with indices of resting cardiac structure and function, vascular stiffness, biochemical and blood-based markers of cardiovascular function, total- and regional body composition, bone mineral density of the lumbar spine and femoral neck, muscle strength, physical function, habitual physical activity, cognitive function, and multidimensional quality of life.

## Methods

### Study design

This study will be a 12-month, community-based, two-arm randomised controlled trial in women with BCa undergoing AC comparing (i) the ability of ExCMR versus resting echocardiography to predict patients who will become functionally disabled following AC; and (ii) the relative effectiveness of a 12-month supervised and structured multi-component exercise program to usual care for preventing functional disability following AC. A total of 100 women with BCa aged 40–75 years who are scheduled to undergo AC will be recruited and randomly allocated to either a 12-month multi-component exercise program (ET, *n* = 50) or a usual care control group (UC, n = 50). All assessments will be performed at the Baker Heart and Diabetes Institute (Melbourne, Victoria, Australia) at baseline (no more than 2-weeks following the commencement of AC), 4-months (~ 3 weeks following the completion of AC) and 12-months from the commencement of AC. A flow diagram of the study protocol is shown in Fig. 1. Where possible, all baseline assessments will be conducted prior to the commencement of AC, however this may not always be possible due to the short time frame between patients being informed of the decision to undergo AC and its commencement. This trial has been approved by the Alfred Hospital Human Research Ethics Committee (Project No: 305/17), is registered with the Australian and New Zealand Clinical Trials Registry (ACTRN12617001408370) and is funded by the World Cancer Research Fund International (Grant IIG_2019_1948).

**Fig. 1 Fig1:**
[figure not shown]
Study CONSORT flow diagram

### Participants

Women deemed eligible to participate in the trial include those aged 40–75 years who have a histologically confirmed diagnosis of breast cancer and are scheduled for anthracycline-based chemotherapy. Participants will be excluded if they have: (1) known structural heart disease including symptomatic ischemic heart disease, significant valvular disease or inherited cardiomyopathies (which would contraindicate AC), (2) a contraindication to CMR such as a pacemaker or implanted metallic foreign body or device, (3) the presence of any serious contraindication or uncontrolled medical condition that would limit participation in the exercise program as outlined in guidelines from the American College of Sports Medicine [44], (4) an inability to complete questionnaires in English language, or (5) significant cognitive impairment (determined by the short portable mental status questionnaire) [45].

### Recruitment and screening

Participants will be recruited via direct referral from surgeons and oncologists from a variety of private and public oncology services around metropolitan Melbourne, Victoria, Australia. Oncology services will be contacted via email with information regarding the study. Group presentations outlining the study rationale, study procedures and eligibility criteria will be organised for oncology services interested in referring potential candidates. Participants identified as potentially eligible by their clinicians will be provided with written material outlining the purpose of the study and requirements of participation prior to being screened over the phone by a member of the research team. Individuals interested in participating will then provide written informed consent after further verbal discussion with a senior investigator.

### Randomisation and blinding

Following baseline testing, each participant will be randomly allocated (1:1 ratio) to the intervention or control group by an independent researcher using a computer-generated, random number sequence with the outcome communicated via telephone. Stratified block randomisation will be used, with participants stratified by age (< 60 or ≥ 60 years) and human epidermal growth factor receptor 2 (HER2) status (positive or negative), with block sizes alternating between two and four participants. Participants, care providers and outcome assessors will not be blinded to group allocation. However, the quantification of all cardiac imaging (echocardiography and cardiac magnetic resonance imaging, CMR) will be performed by researchers blinded to subject identity. Furthermore, outcome assessors will be blinded to pre-chemotherapy values for all assessments.

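### Block sizes that alternate between two and four in an open-label trial leave up to 39% of allocations open to deduction, and this is avoidable

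*Protocol article*

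**What the plan says.** Under Randomisation and blinding, the protocol article states: "Stratified block randomisation will be used". The strata are age (below 60, or 60 and over) and HER2 status (positive or negative), which gives four strata. Participants are to be "randomly allocated (1:1 ratio) to the intervention or control group by an independent researcher", and the blocks are formed "with block sizes alternating between two and four participants".

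The list is held away from study staff. It is a "computer-generated, random number sequence with the outcome communicated via telephone". Allocation comes after the baseline visit: "Following baseline testing, each participant will be randomly allocated".

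The trial is open label: "Participants, care providers and outcome assessors will not be blinded to group allocation". Only the reading of cardiac images is blinded to subject identity, and assessors are blinded to pre-chemotherapy values.

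Under Recruitment and screening, candidates are referred by outside clinicians and receive written material "prior to being screened over the phone by a member of the research team". A senior investigator then holds a further discussion before written consent. Trial status says that recruitment was under way at submission.

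**The concern.** Permuted blocks force balance at the end of every block, so the last allocation of each block follows from the others. Two features make this worse here. The smallest possible block is used, in which every second allocation is determined. The sizes are also said to alternate, so anyone who knows the starting size knows every later block boundary. Because arms are not masked, earlier allocations can become known, and both stratification factors can be known before a woman is randomised.

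An independent allocator on the telephone protects the list. It does not protect against inference from the allocations already released. What is at stake is allocation concealment during screening, consent and the timing of the request for an allocation. If someone involved can deduce the next arm, the order in which two women of the same stratum enter could be influenced without any rule being broken. Whether sizes are disclosed to staff is a detail that an article may leave to the full protocol, so the article's silence on it is no fault. The point rests on what the article does fix: alternating sizes, including blocks of two.

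**Working it through.** The protocol gives no predictability figure to reproduce, so the check is a direct enumeration.

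**Inputs (Randomisation and blinding; sample size from Study design).** Ratio 1:1; block sizes 2 and 4, alternating; four strata; 100 women.

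**Definition.** An allocation is certain when one arm's quota in the current block is already used up, given the block boundaries and the earlier allocations in that stratum.

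**Certain allocations per block.**
- Block of 2 (2 possible orders): probability of certainty by position is 0, 1. Expected number: 1 of 2.
- Block of 4 (6 possible orders): by position 0, 0, 1/3, 1. The third is certain when the first two went to the same arm, which holds for 2 of the 6 orders. Expected number: 4/3 of 4.
- One cycle of both sizes: (1 + 4/3) / (2 + 4) = (7/3)/6 = 7/18 = 38.9%, or about 39 of 100 women.

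**Incomplete last blocks.** The split of women over the strata is not given, so several were assumed: 25/25/25/25, 56/14/24/6, 64/16/16/4 and 50/20/20/10. The certain share is 36% to 39%, whichever size starts.

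**How much the observer must know.** The other knowledge states were simulated with an observer who updates on each allocation:

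| What the observer knows, besides earlier allocations in the stratum | Certain allocations |
|---|---|
| Alternating 2 and 4, starting size known | 38.9% |
| Alternating 2 and 4, starting size unknown | about 25% (strata of 6 or 14), 29% (25), 34% (50) |
| Sizes 2 and 4 in random order, order unknown | about 9% to 11% (strata of 6 to 50) |

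**Larger blocks.** A block of 6 has 3/2 certain allocations. Sizes 4 and 6 with every boundary known give (4/3 + 3/2)/10 = 28.3%. Like for like, that is 38.9 − 28.3 = 10.6 percentage points lower. Randomising the order of sizes 2 and 4 takes the share to about 10%, a larger reduction.

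**Best guess as a second measure.** Guessing the arm that is behind in the block, and tossing a coin when the arms are level, gives an expected 3/2 correct in a block of 2, 17/6 in a block of 4 and 41/10 in a block of 6.
- Sizes 2 and 4: (3/2 + 17/6)/6 = 13/18 = 72.2% correct, against 50% by chance.
- Sizes 2 and 4 in random order: about 71% to 72% in the simulation, so essentially unchanged.
- Sizes 4 and 6: (17/6 + 41/10)/10 = 69.3%.

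Random order therefore removes most of the certainty, but it does little against an informed guess. Larger blocks lower the success of guessing modestly. This is the case for preferring 4 and 6 as well as randomising the order.

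**The case against.** The strongest reply is that 39% is a ceiling. To reach it, someone must know the scheme, know which size starts each stratum and keep a running record for each of four strata. The article gives recruiting staff none of this, and an independent researcher holds the sequence. This stands, and it is why the figure is given as *up to* 39% with the lower values beside it.

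Second, *alternating* may be loose wording for *randomly varied*. If so, the certain share is about 10%. This is possible, but the text does not say it.

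Third, there is limited room to act on a prediction. Referral comes from many outside services, consent and baseline testing precede allocation, and the baseline window is short (no more than two weeks after chemotherapy starts). This reduces the scope without closing it, since screening and consent are done by the study team.

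Fourth, small blocks are a reasonable choice for 100 women over four strata. That is fair as regards balance, but balance does not require a fixed order of sizes.

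A reader might go further and infer that the primary result is at risk, because few events are expected: 36% and 12% of 50 are 18 and 6. The documents do not support this. Nothing in them shows that staff tracked allocations or steered anyone, or how far steering would shift disability at 12 months. Baseline VO2peak is also measured before allocation, and the planned mixed model has repeated time points with a group-by-time term, so steering on fitness would be visible and partly accounted for.

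**Conclusion.** The point holds as a weakness in a stated design rule. As written, up to 38.9% of allocations are certain to an observer who knows the scheme, the starting block and the earlier allocations in the stratum. With the starting size unknown, the share is about 25% to 34%. The first figure is exact for strict alternation with complete blocks; the others are simulated for assumed stratum sizes.

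These are measures of predictability. They are not evidence of selection bias, and no effect on the primary comparison can be derived from the documents. The recommendation rests on the risk being unnecessary and cheap to remove while women are still being randomised.

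**What to change.** For the remaining randomisations, the independent researcher generates a new list within the existing strata, with block sizes in random order, preferably 4 and 6 and with no block of two. The sizes are withheld from the staff who recruit and test. In Randomisation and blinding, *alternating* becomes *randomly varied*, and the publicly stated sizes are left out until recruitment closes. If the sizes were already randomly varied, only the sentence needs correcting.

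The cost is one new list and one changed sentence, plus one change to the analysis. The largest possible imbalance within a stratum rises from 2 (half a block of 4) to 3 (half a block of 6). Age group and HER2 status should therefore be covariates in the primary model. Sample size calculation and statistical analysis does not provide for this now: it plans unadjusted models, and models adjusted for covariates found to differ significantly between groups at baseline.

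If recruitment has closed, the report should state the scheme actually used and who knew it.

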### Cardiopulmonary fitness and functional disability

Cardiopulmonary exercise testing will be used to assess VO_2_peak and functional disability. VO_2_peak, VT and ventilatory efficiency (Minute ventilation to carbon dioxide production slope [VE/VCO_2_ slope]) will be assessed using a continuous ramp protocol on an electronically braked upright cycle ergometer (Lode Excalibur Sport, Lode BV Medical Technology, Groningen, NL) with breath-by-breath expired gas analysis (Vyntus™ CPX, CareFusion, San Diego, CA) in accordance with published guidelines [48]. A flow meter and gas analyser calibration will be performed prior to each test in accordance with the manufacturer guidelines. Two minutes of resting data will be collected prior to the start of exercise, after which participants will undertake a one-minute warm-up at 10–25 W. The workload then increases at a continuous rate of 5–25 W/min until volitional fatigue or symptom limitation. The protocol will be individualised based on each participant’s self-reported physical activity levels, with the aim of reaching volitional exhaustion by 8–12 min. HR and rhythm will be monitored continuously throughout exercise using a 12-lead ECG (Vyntus™ CPX, CareFusion, San Diego, CA) and blood pressure (BP) will be measured every 2 min using an automated cuff (Tango® M2 ECG-gated Automated Blood Pressure Monitor, SunTech Medical Inc., Morrisville, NC). For the purposes of analysis, the test will be considered a peak effort if two of the following criteria are reached: 1) volitional exhaustion; 2) a respiratory exchange ratio > 1.1, and/or 3) > 85% of age-predicted maximal HR [48]. VO_2_peak is defined as the highest 30-s rolling average calculated from six consecutive 5-s VO_2_ epochs. Functional disability will be defined as a VO_2_peak ≤ 18.0 mL/kg/min ref. VT will be assessed using the V-slope method, and the relative proportion of VO_2_peak at which the VT occurs will be used as a measure of changes in submaximal exercise capacity. VE/VCO_2_ slope will be obtained from linear regression analysis of minute ventilation (VE) and expired carbon dioxide (VCO_2_) from the end of the warm-up to the VT [48]. HR and blood pressure (BP) recovery will also be assessed at 1, 2 and 4 min after the end of the test as markers of autonomic function.

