### Total and regional body composition and bone mineral density

#### Dual-energy X-ray absorptiometry

Total and regional fat mass, lean body mass and percentage body fat will be measured from a total body DXA scan (GE Lunar iDXA, GE Healthcare, Little Chalfont, United Kingdom) according to a standardised protocol. Regional composition will be manually assessed using enCore analysis software version 14.10.022 according to standardised procedures. DXA will also be used to quantify areal bone mineral density (g/cm^2^) of the total hip, femoral neck, and lumbar spine (L1-L4 vertebrae).

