#### Magnetic resonance imaging

Muscle volume and muscle fat fraction of the quadriceps in the mid-thigh will be assessed by two-point Dixon-based MRI (Siemens Prisma 3 T MRI) conducted immediately prior to the CMR scans. The two-point Dixon method has been validated as an accurate and reproducible (CV = 0.6%) measurement of muscle-fat content [54, 55]. MRI scans of the dominant thigh will be acquired in the supine position, from the superior patella to the greater trochanter. Images will be transferred to a separate workstation for manual off-line analysis of thigh muscle volume and muscle fat fraction (ImageJ2 v1.52d). Muscle volume will be calculated from the summation of disks method by multiplying the sum of the combined regions of interest by the inter-slice distance. Fat fraction will be calculated from the ratio between the fat and combined fat and water signal intensities for the regions of interest.

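### Blinded quantification is promised for cardiac imaging only, so the manual readings of thigh MRI and regional DXA may be made at 4 and 12 months by people who know the arm

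*Protocol article*

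**What the plan says.** The Randomisation and blinding section sets a general rule: "Participants, care providers and outcome assessors will not be blinded to group allocation". It then qualifies the rule in two ways. The first concerns cardiac images: "the quantification of all cardiac imaging (echocardiography and cardiac magnetic resonance imaging, CMR) will be performed by researchers blinded to subject identity". The second concerns earlier results: "outcome assessors will be blinded to pre-chemotherapy values for all assessments".

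Two measurement sections outside cardiac imaging describe manual work on stored scans:

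- Thigh MRI (Magnetic resonance imaging, under Total and regional body composition and bone mineral density): "Images will be transferred to a separate workstation for manual off-line analysis of thigh muscle volume and muscle fat fraction". The scan is "conducted immediately prior to the CMR scans", so it is a separate acquisition and not part of the CMR examination.
- DXA (Dual-energy X-ray absorptiometry): "Regional composition will be manually assessed using enCore analysis software version 14.10.022 according to standardised procedures".

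Neither section mentions blinding. The Data management section says that the de-identification code is available to members of the research team.

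**The concern.** Manual quantification leaves room for judgement about where a region begins and ends. A reader who knows that a participant trained for a year may, without intending to, resolve doubtful borders in the expected direction. An error of that kind differs by arm. It would enter the between-arm contrast directly, and a larger sample would not average it out.

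Two uses of the data are exposed. Body composition is a secondary outcome compared between arms. In addition, the exploratory outcomes relate change in fitness to cardiac reserve on one side and to four non-cardiac factors on the other. The Background presents the split between cardiac and peripheral protection as an open question with important implications. Cardiac reserve is read blind, while some of the muscle measures set against it need not be.

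**Working it through.** No figure in the protocol bears on this point, so the check is a comparison of sections.

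**Step 1: is the gap stated, or only unmentioned?** It is stated. The general rule is open assessment, and the exception names echocardiography and CMR. Any reading not covered by the exception falls under the rule.

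**Step 2: which off-line readings fall outside the exception?**

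| Reading | How it is made | Covered by the blinded exception? |
|---|---|---|
| 3D echo LVEF and strain | off-line software | yes |
| Exercise and resting CMR, including aortic stiffness | contours and cine analysis | yes |
| Thigh muscle volume and fat fraction | manual, off-line workstation | no |
| Regional DXA composition | manual, analysis software | no |
| Ventilatory threshold (VT) | V-slope; by eye or by software not stated | no |

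**Step 3: does the other safeguard close the gap?** No. Masking to pre-chemotherapy values prevents a reader from steering an individual's change from a known starting point. It does not conceal the arm.

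**Step 4: when does the exposure arise?** Randomisation follows baseline testing, so the baseline scans are acquired before any arm exists. The exposure is at 4 and 12 months. With 100 women and two later visits, that is at most 100 × 2 = 200 thigh MRI scans and 200 DXA scans. With the planned 10% attrition already in effect at both visits it would be 90 × 2 = 180 of each.

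**Step 5: which outcomes depend on these readings?** The exploratory analysis names four non-cardiac factors:

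- central vascular stiffness, taken from CMR and therefore read blind;
- haemoglobin, a hospital laboratory result;
- leg lean mass, from regional DXA, exposed;
- thigh muscle composition, from thigh MRI, exposed.

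Two of the four are exposed.

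**Step 6: is a primary aim touched?** No. Functional disability is derived from VO2peak, which is computed as the highest 30-second rolling average of six consecutive 5-second epochs. The imaging predictors in the second primary aim (LVEF, GLS and peak Qc) are all covered by the blinded exception.

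**The case against.** The strongest case on the other side has four parts.

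*The effect is limited and partly mitigated.* Baseline scans precede randomisation, assessors are masked to pre-chemotherapy values, and the DXA regions follow a standardised procedure. All of this is true and lowers the likely bias. None of it hides the arm from a reader at 4 or 12 months.

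*A journal article condenses the full protocol, which may say more.* That would answer a point resting on silence. Here the article states a rule and lists its exceptions, and as written the rule covers the thigh and DXA readings.

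*The trial relies on objective measurement.* The Usual care group section uses that argument for the primary outcome, to explain why there is no sham comparator. It concerns patient expectancy and does not extend to a reader's judgement on manually analysed images.

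*Stronger readings would overreach.* A reader might infer any of the following, and the documents support none of them:

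- That VT is an equal third case. The article says only "VT will be assessed using the V-slope method" and does not say whether the breakpoint is placed by eye. VT from the baseline and 4-month tests also sets training intensity in the exercise arm, so it has to be read openly for that purpose.
- That peak-effort status could be judged blind from coded traces. One of its criteria, volitional exhaustion, is observed at the test and cannot be recovered afterwards.
- That the whole non-cardiac side of the exploratory analysis is read open. Step 5 shows that two of the four factors are not exposed.
- That the 0.6% CV in the thigh MRI section gives a yardstick for border drift in muscle volume. That CV is for muscle-fat content, a different quantity.
- That the cardiac readers and their file coding could simply take over these scans. The article names different software for each task and does not describe how the cardiac files are coded.

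**Conclusion.** The point holds for thigh MRI and regional DXA. Both are described as manual, both fall under the stated rule of open assessment, and no other section brings them under blinded reading. The consequence is possible observer bias at 4 and 12 months in secondary and exploratory outcomes, including two of the four non-cardiac factors. The primary endpoint, the sample size, the power and the significance level are unaffected.

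The size of the bias cannot be derived from the documents. They give neither an expected effect on muscle or regional composition nor a between-reader error for these manual measures.

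The conclusion assumes that the readers are among the outcome assessors described as open to allocation. The article does not say who reads these scans, so the accurate statement is that they *may* be read with knowledge of the arm. It also assumes that both kinds of scan can be read from coded files. The separate workstation and the analysis software make that likely, but it is not stated.

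**What to change.** In Randomisation and blinding, extend the sentence on blinded quantification to the thigh MRI and the regional DXA analysis. Possible wording to add after it: *Thigh MRI and regional DXA composition will likewise be quantified from stored scans coded for identity, arm and visit, by readers who do not hold the key.*

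In Data management, state that whoever reads these scans has no access to the participant code. At present the code is open to the research team, so relabelling files would not by itself secure blinding.

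The planned readers can stay as they are. The cost is relabelling the stored scans, at most 100 × 3 = 300 of each type over the three visits if baseline is included so that visit is also concealed, and a short delay before reading.

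A separate coded reading of VT for the outcome analysis is optional. It would be a second reading alongside the open one needed for training, and it is worth having only if the V-slope breakpoint is in fact placed by eye.
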